# Study protocol for the sheMATTERS study (iMproving cArdiovascular healTh in new moThERS): a randomized behavioral trial assessing the effect of a self-efficacy enhancing breastfeeding intervention on postpartum blood pressure and breastfeeding continuation in women with hypertensive disorders of pregnancy

**DOI:** 10.1186/s12884-022-05325-3

**Published:** 2023-01-26

**Keywords:** Breastfeeding, Hypertensive disorders of pregnancy, Maternal health, Postpartum cardiovascular health, Self-efficacy

## Abstract

**Background:**

Individuals with hypertensive disorders of pregnancy (HDP) have an elevated lifetime risk of chronic hypertension, metabolic syndrome, and premature cardiovascular disease. Because breastfeeding duration and exclusivity have been associated in observational studies with improved cardiovascular health, optimizing breastfeeding in those with HDP might be an unrealized cardio-prevention approach, in particular because individuals with HDP have more breastfeeding challenges. Breastfeeding supportive interventions targeting one’s breastfeeding self-efficacy have been shown to improve breastfeeding rates.

**Methods:**

We designed an open-label, multi-center 1:1 randomized behavioral trial to test whether a previously validated self-efficacy enhancing breastfeeding intervention can improve breastfeeding duration and/or exclusivity, and lower postpartum blood pressure at 12 months. Randomization is computer-generated and stratified by site (four hospitals in Montreal, Quebec and one hospital in Kingston, Ontario; all in Canada). Included are breastfeeding participants with HDP (chronic/gestational hypertension or preeclampsia) who delivered a live singleton infant at > 34 weeks, speak English or French, and have no contraindications to breastfeeding. Informed and written consent is obtained at hospitalization for delivery or a re-admission with hypertension within 1 week of discharge. Participants assigned to the intervention group receive a breastfeeding self-efficacy-based intervention delivered by a trained lactation consultant in hospital, with continued reactive/proactive support by phone or text message for up to 6 months postpartum. Regardless of group assignment, participants are followed for self-reported outcomes, automated office blood pressure, and home blood pressure at several time points with end of follow-up at 12 months.

**Discussion:**

This study will assess whether an intensive nurse-led behavioral intervention can improve breastfeeding rates and, in turn, postpartum blood pressure – an early marker for atherosclerotic cardiovascular disease. If effective, this form of enhanced breastfeeding support, along with closer BP and metabolic surveillance, can be implemented broadly in individuals lactating after HDP.

**Trial registration:**

ClinicalTrials.gov, # NCT04580927, registered on Oct 9, 2020.

**Supplementary Information:**

The online version contains supplementary material available at 10.1186/s12884-022-05325-3.

## Background

### Long-term cardiovascular risk after hypertensive disorders of pregnancy

Hypertensive disorders of pregnancy (HDP), including chronic hypertension in pregnancy, gestational hypertension and preeclampsia/eclampsia [1] complicate up to 10% of pregnancies worldwide and are significant causes of severe maternal and neonatal morbidity and mortality [2]. Preeclampsia, the most severe HDP, is a complex clinical syndrome characterized by maternal hypertension and other adverse conditions associated with widespread endothelial activation and dysfunction [1, 2]. There is now overwhelming evidence from large observational studies that HDP not only impacts short-term maternal and neonatal health, but are sex-specific risk factors for premature cardiovascular disease, conferring a 3.7-fold increase in the risk of chronic hypertension, a 4.2-fold increase in risk of heart failure, a 1.8-fold increased risk of stroke, and a 2-fold increased risk of premature ischemic heart disease compared with similar individuals with normotensive pregnancies [3]. This risk is apparent at a median of 10–15 years post-affected delivery [4, 5]. Whereas cardiovascular disease risk is partly mediated by the development of hypertension and metabolic syndrome [6–9], there is evidence of persistent subclinical endothelial dysfunction for months to years following pregnancy affected by HDP, contributing to accelerated vascular impairment [10–13] (Fig. 1). The postpartum period has thus been identified as a critical opportunity to implement targeted screening and positive health interventions for those affected by HDP, and contemporary clinical practice guidelines now encourage systematic assessment of cardiovascular risk post-HDP [14, 15].

**Fig. 1 Fig1:**
[figure not shown]
Hypothesized mechanism of cardiovascular protection of breastfeeding in women with hypertensive disorders of pregnancy. Conceptual diagram depicting associations between maternal hypertensive disorders of pregnancy and cardiovascular health, and hypothesized mediation by breastfeeding. Photos used in Fig. 1 were downloaded from iStock through a subscribed account. All photos have a Standard License, meaning we have the right to use the photos in perpetuity, and are referenced in Fig. 1

### Breastfeeding for maternal cardiovascular health

The significant benefits of breastfeeding for both infants and mothers are well-documented [16], and global recommendations for optimal infant health are to breastfeed exclusively for the first 6 months of life and to continue breastfeeding (along with appropriate complementary solid foods) for up to 2 years or beyond [17]. Although breastfeeding promotion typically focuses on infant nutrition, the optimal “dose” of breastfeeding to benefit maternal health is unknown. For example, observational data suggest that breastfeeding can lower maternal blood pressure (BP), risk of metabolic syndrome, and other markers of cardiovascular risk [18] both in the short term [19, 20] and long term [21, 22]. A recent meta-analysis including more than 1.1 million parous individuals from eight large observational studies concluded that any breastfeeding is associated with an approximately 10% lower risk of fatal and non-fatal cardiovascular disease or stroke as compared with no breastfeeding, with a progressive risk reduction for all cardiovascular disease outcomes with lifetime durations of breastfeeding [23]. Putative mechanisms include lowering of BP and metabolic syndrome [18] in the short term [19, 20] and long term [21, 22], possibly by helping to re-set the metabolic changes of pregnancy. Potential pathways for the “re-set hypothesis” include mobilization of stored fat after delivery, reestablishment of glucose homeostasis, and mobilization of lipids for milk synthesis [24, 25]. Mechanistic studies have also begun to uncover the cardiovascular role of oxytocin, the lactation hormone responsible for the milk-ejection reflex. Functional oxytocin receptors have been found in vascular beds and in the myocardium in both animals and humans, and oxytocin has been shown to have pleiotropic cardioprotective effects including systemic vasodilation and angiogenesis of smooth muscle and endothelial cells, as well as antioxidative and anti-inflammatory effects [26–28]. An inverse relationship between lactation duration and subclinical atherosclerosis (as indicated by carotid lumen thickness or aortic and coronary calcification) has also recently been identified [29–31], adding to explanations for how breastfeeding may influence BP and the development of cardiovascular events.

While few studies have specifically examined the relation between breastfeeding and postpartum BP after HDP, available evidence suggests a possible robust effect. A US study of 246 individuals with early or late-onset HDP who were 4 to 6 weeks postpartum found a mean decrease of 5.3 mmHg systolic (*p* = .03) and 3.6 mmHg diastolic BP (*p* = .04) among those who were lactating (*N* = 78) compared to non-lactating (*N* = 69) [32]. Another US study of 379 individuals with HDP demonstrated a mean decrease of 16.3 mmHg systolic/16.8 mmHg diastolic BP among those with gestational hypertension who breastfed for more than 6 months compared to no breastfeeding, adjusting for pre-pregnancy body mass index and other factors [33]. A Canadian cross-sectional analysis of postpartum BP and metabolic markers in 622 individuals with HDP and other pregnancy complications similarly found an 11% reduction in metabolic markers and a 6 mmHg decrease in median systolic BP among those who breastfed for more than 6 months compared to no breastfeeding, after adjusting for potential confounders [34]. While these observations warrant replication, the BP reductions associated with lactation exceed those seen with either weight loss [35] or antihypertensive pharmacotherapy [36].

### Breastfeeding for infant neurodevelopment after exposure to HDP

Infant brain development is a dynamic process beginning in utero that is affected by genetic, epi-genetic, and environmental factors [37]. It has been postulated that exposure to a hypertensive intrauterine environment can disrupt fetal brain development by impairing placental perfusion. A number of studies have demonstrated that fetal exposure to maternal HDP is associated with poorer neonatal neurodevelopmental compared with no such exposure [38, 39], although the mechanism for this association is not well described. Gestational age at birth and infant feeding patterns are likely important mediating factors that have not been universally accounted for in studies linking HDP with neurodevelopment [40]. However, a recent large observational study showed an increased risk of cerebral palsy, autism, epilepsy, and attention deficit hyperactivity disorder in children exposed to term preeclampsia compared with no preeclampsia [41–46], suggesting a direct effect of preeclampsia on neurodevelopment independent of gestational age. Moreover, longer breastfeeding duration has been shown to be positively associated with better motor, language and cognitive skills in infants [47]. Therefore, there is biological plausibility that breastfeeding in infants born to those with hypertension is potentially strongly protective.

### Breastfeeding rates in individuals with HDP

Despite the potential maternal and infant benefits of breastfeeding, the limited evidence available demonstrates that individuals with HDP have lower rates of breastfeeding initiation, duration and exclusivity compared to those with normotensive pregnancy [48–52]. For example, a German study of 1500 deliveries (877 with HDP) found that only 39.2% of those with HDP initiated breastfeeding compared to 48.9% of matched controls without HDP (*p* < 0.001) [48]. However, the difference in breastfeeding continuation to 3 months was smaller (37.2% in those with HDP versus 42.2% in those without), underscoring the importance of supporting successful initiation of lactation among those with HDP who intend to breastfeed [48]. A US survey of 5285 postpartum persons reported that those with HDP (*N* = 754) were significantly less likely to initiate lactation (82% vs. 87%) or to provide their infant with breastmilk for at least 8 weeks (48% vs. 55%) than those without HDP [49]. A Brazilian prospective cohort study comparing individuals with gestational hypertension (*N* = 42) to normotensive controls (*N* = 124) found that those with hypertension were significantly more likely to supplement their infants with formula during postpartum hospitalization (*p* < .00001) and to cease exclusive breastfeeding or wean by 6 months after controlling for mode of delivery, parity, and gestational age at birth, suggesting greater difficulties with maintenance of lactation over time [50].

Several potential barriers to successful breastfeeding among those with HDP have been identified, including higher rates of caesarean delivery and preterm birth; maternal-infant separation and delayed initiation of lactation; the impact of HDP medications (e.g., diuretics, magnesium sulfate) on milk production; and underlying endocrine factors (e.g., obesity, diabetes, metabolic syndrome) that may influence lactogenesis [49, 50, 53]. There may be additional under-studied biologic and psychosocial factors influencing lactation post-HDP related to the flux of reproductive hormones associated with breastfeeding (including androgens, cortisol, oxytocin and prolactin), which may moderate the risk of adverse psychological states and chronic hypertension after delivery. For example, changes in maternal androgen levels have been linked to postpartum depression [54]. Androgens have also been shown to have effects on the vascular system that are very similar to the changes observed in hypertension, including increases in vascular tone, hypercoagulability and platelet aggregation [54–58]. Psychological distress after delivery may further increase risk of hypertension by disrupting cortisol function and the hypothalamo-pituitary-adrenal (HPA) axis [59, 60]. Declines in oxytocin may impact both maternal mood and maternal insulin sensitivity and cardiovascular function [61, 62]. Finally, prolactin (the hormone responsible for milk synthesis) also appears to carry actions directly antagonistic to those of insulin, which may contribute to the metabolic changes that occur during pregnancy [63]. These hormones of lactation have also been implicated in postpartum depression [64], which may be an important mediator between HDP and low breastfeeding rates.

### Targeting breastfeeding self-efficacy to increase breastfeeding outcomes

Systematic reviews of breastfeeding supportive interventions demonstrate a significant positive impact of individual-level support on rates of breastfeeding duration and exclusivity to 6 months postpartum among healthy term infants [65, 66]. Among healthy parents, breastfeeding support interventions targeting the modifiable factor of breastfeeding self-efficacy (BSE) have been associated, in particular, with increased rates of breastfeeding duration and exclusivity [67, 68]. Derived from Bandura’s social cognitive theory, breastfeeding self-efficacy refers to a persons’ confidence in their perceived ability to breastfeed their infant, and is influenced by four main sources of information (performance accomplishments, vicarious learning, verbal persuasion, and physiological/affective states) [69]. Co-investigator [name] developed and validated the 33-item Breastfeeding Self-Efficacy Scale (BSES) [70] and 14-item BSES-Short Form [71], which has also been adapted into a validated measure of BSE among parents with ill or preterm infants [72]. BSE has long been identified as a potent predictor of breastfeeding duration and exclusivity in diverse populations [73–77]. A meta-analysis of interventions to improve BSE found that participants in intervention groups had significantly higher BSE (scoring 4.86 points higher at 2 months postpartum) and that the odds of exclusive breastfeeding at 2 months increased by 10% in the intervention groups for each 1-point increase in mean BSE score between intervention and control groups [67]. Moreover, BSE-focused interventions were most successful when delivered in both hospital and community settings using multiple contact points [67]. Although several studies have underscored the need for enhanced breastfeeding support for those with HDP [51–53], interventions designed to increase breastfeeding self-efficacy have not yet been tested specifically in this population. Individualized support targeting self-efficacy may help those with HDP overcome their unique breastfeeding challenges, as well as enhance parental engagement in other lifestyle interventions (e.g., weight loss, exercise, healthy eating) which have been shown to decrease cardiovascular risk post-HDP [78].

### Supportive pilot data

Feasibility and acceptability of the randomized control behavioral trial (RCT) procedures and the breastfeeding self-efficacy intervention (BSEI) were determined in a single-center pilot RCT conducted between February 2019 and November 2020, entitled Breastfeeding and blood Pressure patterns in MOthers with recent hypertensive coMplications of pregnancy (BP-MOM study, ISRCTN.com, # 18352227, registered on Jan 29, 2019). Of 183 individuals with HDP screened for study eligibility, 90 met the inclusion criteria and were approached. Of these, 45 agreed to participate, completed baseline measures and were randomized to usual care (*N* = 21) or the BSEI (*N* = 24) [79]. Follow-up to the 6-month clinic appointment was completed by 37 (82%) participants. Follow-up to 12 months was interrupted by the first wave of the COVID-19 pandemic, and was conducted predominately remotely due to public health restrictions (*N* = 27, 80% completed remote and *N* = 7, 20% completed in person 12-month follow-up).

Mean systolic BP was lower at all time-points in the intervention group than the usual postpartum care group (Table 1), as was number with BP in the hypertensive range, and number requiring anti-hypertensive therapy (Fig. 2).

**Table 1 Tab1:** BP-MOM mean systolic and diastolic blood pressure at each time point in postpartum women with HDP

	Total	Breastfeeding Intervention	Usual Postpartum Care	*p*-value
N	45	24	21	
Baseline systolic (m, sd)	129 (11.3)	127 (11.8)	132 (10.5)	.29
Baseline diastolic (m, sd)	82 (8.9)	80 (10.3)	85 (6.0)	.11
N	36	18	18	
3-month systolic (m, sd)	115 (12.1)	115 (11.9)	116 (12.5)	.77
3-month diastolic (m, sd)	74 (8.4)	72 (8.3)	75 (8.4)	.29
N^a^	31	15	16	
6-month systolic (m, sd)	113 (11)	112 (12.3)	114 (10)	.70
6-month diastolic (m, sd)	72 (10.2)	71 (11.7)	73 (8.7)	.56
N^b^	29	13	16	
12-month systolic (m, sd)	118 (13)	117 (10.1)	119 (15.3)	.75
12-month diastolic (m, sd)	76 (9.6)	77 (9.8)	76 (9.7)	.61

^a^ Data at 6-month time point does not reflect full sample size as in-person visits were limited due to the COVID-19 pandemic. ^b^ Blood pressure values at 12-months were derived from both home blood pressure measurements (self-reported) and in person automated office blood pressure measurements due to restrictions for in-person visits during the COVID-19 pandemic

**Fig. 2 Fig2:**
[figure not shown]
Elevated Blood Pressure or Use of Anti Hypertensive Medication in Post Partum Women with HDP. This figure shows mean participant blood pressures according to study allocation group (breast feeding self-efficacy based intervention or usual postpartum care) at each of the study time points from the feasibility study “Breastfeeding and Blood pressure patterns in MOthers with hypertensive coMplications of pregnancy (BP-MOM)”. Elevated blood pressure was defined as average automated office blood pressure > 140/90 mmHg or average home blood pressure > 135/85 mmHg

In addition, mean breastfeeding self-efficacy scores (out of a total of 70) were higher in the intervention compared to the control group at 6 weeks (54.7 +/− 9.5 vs. 46.1 *+/−* 13.1), 3 months (55.3 +/− 13.9 vs. 46.3 +/− 15.9) and 6 months (57.2+/− 12.9 vs. 50.3 +/− 18.3). Compared with participants in the usual care group, those who received the BSEI were more likely to be breastfeeding exclusively at 6 weeks (71.4% vs. 44.4%) and 3 months (72% vs. 37%), and to continue breastfeeding to at least 6 months (90% vs. 58%).

The vast majority of participants assigned to the intervention group reported good or very good overall satisfaction with the BSEI at both 3 months (95%, *N* = 19) and 6 months (94%, *N* = 17). Given the positive outcomes and high acceptability of the BSEI, a recruitment rate of 50% within a high-risk obstetrical population, and participant retention of 82% at 6 months, our research team’s steering committee agreed that proceeding with a larger trial was warranted with a protocol adapted for COVID-19 pandemic contingencies (e.g., incorporating options for remote recruitment and measurements).

### Summary and rationale

Although individuals with HDP are at substantial risk for chronic hypertension, metabolic syndrome, and premature cardiovascular disease (CVD) and may benefit in particular from the cardiometabolic effects of breastfeeding, they face additional lactation challenges (Fig. 1). BSE-based supportive interventions have shown promise in improving breastfeeding rates, and our single-centre pilot data further supported a metabolic trend in the parent. There are existing knowledge gaps as to the optimal strategy to optimize breastfeeding and improve postpartum cardiometabolic health in this population, which we hope to address with the sheMATTERS study.

## Methods

### Study objectives and hypotheses of sheMATTERS

The overall aim of the sheMATTERS (iMproving cArdiovascular healTh in new moThERS) trial is to assess the impact of an individualized BSEI on postpartum blood pressure and breastfeeding rates among patients with HDP who initiated breastfeeding. Longer-term (15-year) post-trial follow-up of study participants will additionally be conducted, to observe whether breastfeeding support, and breastfeeding duration/intensity helps to lower the incidence of chronic hypertension or other cardiovascular risk factors, as well as heart disease, stroke, and other long-term health issues among those with HDP (Fig. 3).

**Fig. 3 Fig3:**
[figure not shown]
sheMATTERS Study Schemata. Schema of the sheMATTERS randomized behavioral trial design, additional comparison group, and long-term pragmatic cohort

The primary study objective is to assess whether the BSEI will result in lower systolic and/or diastolic BP, or a lower need for antihypertensive therapy at 12 months postpartum. Secondary study objectives are to 1) assess whether the BSEI will result in higher rates of exclusive and any breastfeeding at 6 months, as well as continued breastfeeding to 12 months; 2) assess whether the BSEI will decrease the rate of having metabolic syndrome at 12 months postpartum; 3) explore maternal blood pressure trajectories over time according to ‘dose’ of breastfeeding; 4) evaluate whether those who breastfeed for longer are more likely to engage in other cardiovascular protective behaviors, such as weight reduction, healthy eating, and higher levels of physical activity at 6 and 12 months postpartum; 5) explore the biological and psychosocial determinants of breastfeeding behavior to 12 months postpartum among those with HDP; and 6) collect bio-samples to measure key inflammatory and angiogenic factors from participants who recently had HDP to advance our understanding of the different phenotypes of these individuals and their associated cardio-metabolic risk in the short and long-term.

### sheMATTERS trial hypotheses

The primary study hypotheses are that 1) individuals with HDP who receive the BSEI will have lower BP (approximately 5 mmHg systolic and/or 2 mmHg diastolic) compared to those who do not breastfeed, and 2) individuals with HDP who receive the BSEI will have a lower demand for antihypertensive treatment at 12 months postpartum compared with those who receive usual postpartum care. The secondary hypotheses are that:there will be a modest (10–20%) relative benefit in breastfeeding outcomes among participants with HDP who receive the BSEI compared to those who receive usual postpartum care;there will be a lower rate of metabolic syndrome in participants with HDP who receive the BSEI compared to those who receive usual postpartum care, and a greater difference when compared to those who do not breastfeed;rates of breastfeeding duration and exclusivity will be correlated with a greater tendency towards more cardioprotective behaviors over 12 months postpartum;infant neurodevelopment will be positively correlated with longer duration of any breastfeeding;severity of HDP, obesity, markers of inflammation, as well as education level and psychological symptoms at birth will be correlated with breastfeeding duration and exclusivity over 12 months postpartum.

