### Participants and recruitment

We are recruiting eligible postpartum (*N* = 278) breastfeeding parents with HDP into the RCT to assess the effect of the BSEI on BP and breastfeeding outcomes. In addition, we are recruiting (*N* = 45) non-breastfeeding parents with HDP into a non-randomized observational arm of the study, serving as a comparison group. Inclusion criteria include: having a diagnosis of HDP, as per the 2018 International Society of Hypertension in Pregnancy (ISSHP) classifications [80], age ≥ 18 years, singleton live birth delivered at ≥34 weeks gestation, speaks and understands English or French, has cellular phone and internet access, has a valid health insurance card at time of recruitment, and (for those in the randomized arm), intends to breastfeed and initiates breastfeeding or milk expression prior to hospital discharge. Exclusion criteria include: maternal intensive care unit admission lasting > 24 hours, severe or uncontrolled psychiatric illness that would preclude active engagement in the study, active COVID-19 infection at time of postpartum hospitalization, or previous participation in the trial’s pilot study. In addition, breastfeeding individuals are excluded from the randomized arm if they or their infant have any absolute contraindication to breastfeeding (e.g., HTLV-1 infection; galactosemia) or conditions that may interfere with successful initiation of breastfeeding (e.g., history of breast reduction surgery; infant with cleft palate).

Potential participants are identified and recruited from the hospitals’ antenatal, intrapartum or postpartum units by trained research assistants. Participants may also be referred antenatally to the research team by their obstetrical care provider or self-refer in response to recruitment posters and flyers distributed in the participating centers. The research staff meet with interested participants in person or via telephone to assess eligibility, and obtain informed verbal and written consent (see Additional file 5: Appendix 2). All eligible persons, including those who decline participation in the RCT or observational arms of the study, are additionally invited to participate in an independent long-term passive follow-up study via electronic health record data linkage.

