### Randomization procedures

After giving birth, all eligible and consenting postpartum individuals who are planning to breastfeed are enrolled in the RCT and randomly allocated by the research assistant to either the control group (usual in-hospital and community postpartum care only) or intervention group (usual in-hospital and community postpartum care plus the BSEI with an assigned lactation specialist). A usual care group as a primary comparison arm is best suited to assess the effectiveness of a behavioral intervention. A central random allocation sequence is computer-generated (via REDCap) stratified by study site, with an allocation ratio of 1:1 using random block sizes of 2, 4 and 6. Allocation is concealed to all research team members until randomization. The research assistant informs the participants of their group allocation immediately after they’ve completed their baseline measures. Although the RCT participants cannot be blinded, data oversight and analysis will be performed by research personnel blinded to group allocation.

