### Sample size calculation

In order to detect a 5 mmHg between-group differences in postpartum blood pressure and in breastfeeding rates, we are aiming to recruit an approximate of 323 participants (after accounting for a 30% loss to follow-up). Around 278 of these participants (86%) will be randomized to either the breastfeeding intervention group or breastfeeding control group, and 45 participants (14%) who will not be breastfeeding will serve as a comparison group in the observational arm of the study. Accounting for annual delivery rates at each of the study sites and assuming that ~ 8% of deliveries are affected by HDP at all sites, and 70% of those will initiate breastfeeding (an average of general Canadian population initiation rate of ~ 90%, German HDP population rate of 40%, and United States rate of 82% in those with HDP) [48, 94] we anticipated reaching our recruitment target over a two-year period, without accounting for additional recruitment delays due to the pandemic.

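### The added metabolic-syndrome claim against non-breastfeeding women compares only usual care with a self-selected group, so it gives no evidence about the intervention

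*Protocol article*

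**What the plan says.** The section on trial hypotheses gives the metabolic-syndrome hypothesis in two parts. The first is the randomized contrast: "there will be a lower rate of metabolic syndrome in participants with HDP who receive the BSEI compared to those who receive usual postpartum care". The second adds "and a greater difference when compared to those who do not breastfeed".

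The matching secondary objective covers the first part only: "assess whether the BSEI will decrease the rate of having metabolic syndrome at 12 months postpartum".

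Under Participants and recruitment, the 45 non-breastfeeding women enter "into a non-randomized observational arm of the study, serving as a comparison group". In the Background, the section on breastfeeding rates in HDP lists, among potential barriers to breastfeeding, "underlying endocrine factors (e.g., obesity, diabetes, metabolic syndrome) that may influence lactogenesis".

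The Statistical analysis section places metabolic syndrome among the characteristics and outcomes to be compared by two-sample tests. It names no other analysis for this outcome and no criterion for the greater difference.

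**The concern.** Read as a whole, the hypothesis suggests graded support for the intervention: some benefit against usual care, and more against no breastfeeding. Both differences share the BSEI arm, so the step from one to the other carries no information about the BSEI. It compares usual-care participants, who had to intend and initiate breastfeeding, with women who did not breastfeed. On the article's own account of barriers to breastfeeding, the second group may be metabolically worse from the outset. A difference due to selection could then be reported as part of a confirmed hypothesis about the intervention.

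**Working it through.** **Inputs from the article**
- Randomized: "Around 278 of these participants (86%) will be randomized", "with an allocation ratio of 1:1 using random block sizes of 2, 4 and 6", so 278 / 2 = 139 per arm.
- Non-breastfeeding group: 45. Check: 278 + 45 = 323, the stated total, with shares 86.1% and 13.9%, as stated.
- Loss to follow-up 30% (Sample size calculation): 139 × 0.7 ≈ 97 per arm and 45 × 0.7 ≈ 31 non-breastfeeding.
- The article gives no metabolic-syndrome rates. All rates below are assumptions.

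**Step 1: algebra.** Let pB, pU and pN be the 12-month rates with BSEI, usual care and no breastfeeding. The first half predicts a lower rate, which fixes the sign, so the second clause is

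(pN − pB) > (pU − pB), which reduces to pN > pU.

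On the ratio scale, pB/pN < pB/pU also reduces to pN > pU, and odds ratios give the same ordering. In 1,000,000 simulated trials with 97/97/31 women, the clause coincided with pN > pU (observed rates) every time. With pU = pN = 20%, its probability stayed at 0.479 for BSEI rates of 10%, 20% and 30%.

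**Step 2: how often the clause alone is met.** The probability was enumerated exactly from two binomials, under two possible ways of judging it: the order of the observed rates, and a pooled z-test of pN > pU at one-sided 2.5%.

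| pU | pN | Order, 97 vs 31 | Test, 97 vs 31 | Order, 139 vs 45 | Test, 139 vs 45 |
|---|---|---|---|---|---|
| 10% | 10% | 0.488 | 0.032 | 0.490 | 0.029 |
| 20% | 20% | 0.479 | 0.029 | 0.480 | 0.028 |
| 30% | 30% | 0.504 | 0.029 | 0.503 | 0.027 |
| 20% | 25% | 0.703 | 0.096 | 0.741 | 0.116 |
| 20% | 30% | 0.859 | 0.224 | 0.902 | 0.296 |
| 20% | 40% | 0.982 | 0.603 | 0.994 | 0.752 |

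The BSEI rate does not enter any cell. A formal test lowers the error rate when pN = pU, but it still tests pN > pU.

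**Step 3: the full two-part hypothesis.** Both halves were judged by order of observed rates, with 97/97/31 women.

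| pB | pU | pN | First half | Second half | Both |
|---|---|---|---|---|---|
| 10% | 20% | 30% | 0.97 | 0.86 | 0.83 |
| 20% | 20% | 30% | 0.46 | 0.86 | 0.37 |
| 30% | 20% | 30% | 0.04 | 0.86 | 0.03 |
| 20% | 20% | 20% | 0.46 | 0.48 | 0.17 |

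All the sensitivity to the BSEI comes from the first half. The second half stays at 0.86 whether the BSEI helps, does nothing or harms.

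**The case against.** **No decision rule is stated.** The section lists expected directions and does not say that the order of point estimates confirms anything. The analysis the article names is two-sample tests. This stands. A reader might infer that the hypothesis is confirmed about half the time by chance. The article does not support that: the figure needs pN = pU, a point-estimate rule that is not stated, and the second clause taken alone. Under a one-sided 2.5% test it is about 3%.

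**The clause is half of a conjunction.** This stands too. A reader might infer that the hypothesis would be met as often under a useless or harmful BSEI as under an effective one. Step 3 shows otherwise: 83%, 37% and 3% for benefit, no effect and harm. The insensitivity belongs to the added clause only.

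**The wording might mean only that BSEI versus non-breastfeeding is tested directly.** Then the quantity is pN − pB and the BSEI rate does not cancel. At pN = 30%, a one-sided 2.5% test with 97 against 31 women is met in 75%, 22% and 3% of trials for BSEI rates of 10%, 20% and 30%. This reading still rests on the non-randomized group: a BSEI with no effect succeeds in 22% of trials under a 10-point selection gap and in 60% under a 20-point gap (20% against 40%).

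**Selection is not quantified.** Correct. The Background speaks of potential barriers, not established causes, and the size of any gap is assumed here. Nor is adjustment impossible. Waist circumference is first recorded at 6 months, but Table 2 has height, weight, blood tests and medical history at baseline.

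**The objective is already confined to the BSEI effect and the group is labelled observational.** Both are true, and they favour bringing the hypothesis into line with them.

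**Conclusion.** The point holds for the added clause, not for the whole hypothesis. The cancellation is exact and needs no assumption beyond the sign that the first half fixes. The clause therefore gives no evidence about the BSEI, and would give none even with an ideal non-breastfeeding control group. The exposure to selection has support in the article as to direction. Its size rests on assumed rates: gaps of 10 to 20 points raise the chance that the clause is met from 48–50% to 86–98% by order of estimates, and from about 3% to 22–60% by a one-sided 2.5% test (97 against 31 women). What is at stake is the interpretation of one secondary hypothesis. The randomized contrast on metabolic syndrome and the primary analysis are unaffected. Minor to moderate.

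**What to change.** State the secondary hypothesis as BSEI versus usual care only, reported as a risk difference with 95% CI, adjusted for site. Report metabolic syndrome in the non-breastfeeding group as a separate observational contrast of breastfeeding with no breastfeeding, adjusted for baseline BMI, diabetes and HDP type, and say that it is not evidence for the BSEI.

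The cost is a change of wording and one analysis specification. Height, weight and medical and obstetrical history are already collected at baseline, so no new data should be needed. The trial gives up one secondary claim. The observational contrast will be imprecise with about 31 to 45 non-breastfeeding women. For example, at assumed rates of 20% in 194 breastfeeding women (2 × 97) and 30% in 31 others, the unadjusted 95% CI is about ±1.96 × √(0.16/194 + 0.21/31) ≈ ±17 points.
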